### Sample Size Calculation

The sample size was estimated using hs-CRP. Currently, the hs-CRP of NSTEACS decreased from 5.30 mg/L to 3.74 mg/L after 14 days of conventional treatment, with a decline rate of 29.43% (26). The hypothesis is that the treatment group could reduce the hs-CRP of NSTEACS by 35%. With a type I error rate of α = 0.05 and a power of 80% (a type II error rate of β = 0.2), one arm requires a sample size of 27. With a 20% drop-out rate, we have to recruit a total of 66 patients. The following is the formula for calculating sample size (27):

$$\begin{array}{l} \text{n}=2{\left[\frac{\left({\text{u}}_{\alpha }+{\text{u}}_{\beta }\right)}{\delta /\sigma }\right]}^{2}+\frac{1}{4}u_{\alpha }^{2} \end{array}$$

n, is the sample size required in each group, δ = μ_1_-μ_2_, is the difference between means of two groups, σ, is the standard deviation, u_α_ and u_β_ are the values of u corresponding to the test level α and type II error probability β, respectively.

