### Statistical Analyses

An independent biostatistician will perform statistical analysis. The result of recruitment, the specific reasons for data missing and the distribution of each statistical analysis data set will be described. The primary outcome, the change values of hs-CRP from recruitment to day 7 ± 3, day 14 ± 3 and the day of revascularization, and the secondary outcome, the change scores in five dimensions of SAQ at the same time, are both continuous variables. For comparison between groups, the continuous variables will be described using means ± SD, median, interquartile range, etc., and the Shapiro-Wilk normality test and Levene test for variance homogeneity will be performed. A Student *t* test will be used to compare two groups that have a normal distribution with homogeneous variance, otherwise the Wilcoxon rank-sum test will be used. When some continuous variables are converted into categorical variables, these categorical variables will be described using rates, and the chi-square test or Fisher's exact probability method will be used. For comparison within groups, the paired *t* test or Wilcoxon signed-rank test will be used for continuous variables and the McNemar test for categorical variables. If there are baseline imbalances, Cox regression analysis, logistic regression and multivariate analysis of covariance will be used to adjust confounding variables. The longitudinal data with repeated measures will be analyzed using the linear mixed-effects model to assess associations. The safety analysis will tabulate a detailed description of the adverse reactions, adverse events and serious adverse events and compare the difference in incidence between two groups using Fisher's exact probability method. A difference of *P* < 0.05 at two-tailed test will be considered statistically significant in all analyses. The statistical analyses will be performed using SAS software version 9.4 (SAS Institute, Cary, NC, USA).

After metagenomic sequencing is completed, microbiota community structures will be compared at different taxonomic levels. The abundance and diversity of intestinal flora will be analyzed. The relationship between microbiota composition and clinical outcomes will be investigated using univariate and multivariate linear and nonlinear mixed and regression models. Gene annotation will be conducted to study the function of the intestinal flora.

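### The primary hs-CRP test is picked from the data and run on raw mg/L change, while the hypothesis is a percentage fall; one baseline-adjusted log-scale analysis should be fixed in advance

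*Protocol article*

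**What the plan says.** Under Statistical Analyses, the protocol article defines the primary outcome as the change in hs-CRP from recruitment. No log or percentage transformation is stated. For the between-group comparison, "the Shapiro-Wilk normality test and Levene test for variance homogeneity will be performed". The Student t test is then used for two groups with a "normal distribution with homogeneous variance, otherwise the Wilcoxon rank-sum test will be used". Covariate adjustment is planned only if baseline imbalance is found. A linear mixed-effects model is mentioned for the repeated measurements, but it is not named as the primary analysis and no scale is given for it.

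Under Sample Size Calculation, the planning figures are on a percentage scale. Under conventional treatment hs-CRP "decreased from 5.30 mg/L to 3.74 mg/L after 14 days of conventional treatment, with a decline rate of 29.43" per cent. For SQSX, "The hypothesis is that the treatment group could reduce the hs-CRP of NSTEACS by 35" per cent. The formula uses a difference between two means divided by an SD. The SD is defined as a symbol ("σ, is the standard deviation") but has no value.

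**The concern.** Three choices do not fit together.

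- **The test depends on the outcome data.** The t test addresses a difference in mean mg/L change; the rank-sum test addresses a shift in ranks. Which question the trial answers is settled only after the pretests have been run. The rank-sum branch also does not deal with unequal variances, although a failed Levene test sends the analysis there.
- **The scale differs from the hypothesis.** A 35% against a 29.43% fall is a proportional effect. Raw change turns it into an effect in mg/L that varies with each patient's baseline.
- **Baseline is used only as the starting point of the change.** Adjustment for baseline hs-CRP depends on an observed imbalance, so the precision it would bring is not secured in advance.

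At stake are a primary result that may not translate back to the planning figures and, if hs-CRP is skewed, a substantial loss of power in a trial planned on 27 patients per arm.

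**Working it through.** **1. Inputs.** From Sample Size Calculation: α = 0.05, power 80%, baseline 5.30 mg/L, control day-14 value 3.74 mg/L, SQSX fall 35%, n = 27 per arm. From Statistical Analyses: two-sided testing. Assumed, because the documents give no figures: lognormal hs-CRP, the same log SD at both times, and the correlation between log baseline and log day 14.

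**2. The plan's own figures.**
- Control fall: (5.30 − 3.74)/5.30 = 29.43%, which reproduces.
- n = 27 cannot be checked without σ. Solving the plan's formula, 27 = 2[(1.960 + 0.842)/(δ/σ)]² + 1.960²/4, gives δ/σ = 0.776.
- δ = 5.30 × (0.35 − 0.2943) = 0.295 mg/L, so the implied σ is 0.295/0.776 = 0.38 mg/L.

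**3. The scale.** The planned between-arm ratio at day 14 is 0.65/0.7057 = 0.921, the same for every patient on the log scale. In mg/L the benefit is 0.0557 × baseline: 0.295 at a baseline of 5.30, and twice that (0.59) at a baseline of 10.60.

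**4. Simulation.** 27 per arm, baseline mean 5.30, control day-14 mean 3.74, 2,000 trials per setting (4,000 with no effect).
- *Plan's rule:* t test on raw change if both arms pass Shapiro-Wilk and Levene passes, each at 0.05; otherwise rank-sum test on raw change.
- *Log-ANCOVA:* log(day 14) = a + b·arm + c·log(baseline).

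| SQSX/placebo ratio | Log SD | Correlation | Plan's rule | Log-ANCOVA |
|---|---|---|---|---|
| 0.65 (assumed) | 0.6-1.0 | 0.3-0.7 | about 15-55% | about 36-96% |
| 0.65 (assumed) | 0.8 | 0.5 | 26% | 60% |
| set for about 80% with log-ANCOVA | 0.3-1.0 | 0.3-0.85 | 32-44% | 77-81% |
| 0.921 (protocol) | 0.6-1.0 | 0.3-0.7 | 5-9% | 6-11% |
| 0.921 (protocol) | 0.3-1.0 | 0.5-0.7 | 4-17% | 6-29% |
| 1 (no effect) | 0.5-1.0 | 0.5 | 4.5-4.9% | 4.9-5.4% |

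A between-arm ratio of 0.65 is not the protocol's effect. It means an SQSX mean of 0.65 × 3.74 = 2.43 mg/L, a fall of (5.30 − 2.43)/5.30 = 54%.

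**5. Where the loss arises.** At log SD 0.8 and correlation 0.5, with the effect set for about 80% power with log-ANCOVA (ratio 0.584):

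| Analysis | Power |
|---|---|
| t test, raw change | 27.3% |
| Rank-sum test, raw change | 37.9% |
| Plan's pretest rule, raw change | 37.8% |
| ANCOVA, raw hs-CRP | 67.4% |
| t test, log change | 68.8% |
| ANCOVA, log hs-CRP | 81.4% |

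The rule matches the plain rank-sum test and beats the plain t test, so the pretests are not what loses power. Moving to log change takes 37.8% to 68.8%; adjusting for log baseline takes it to 81.4%.

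**6. If raw change is normal.** With a standardised difference of 0.776 and 27 per arm, the rule has 79.1% power and the plain t test 79.4%. The rule goes to the rank-sum test in 14% of such trials. In the lognormal settings of step 5's calibration (log SD 0.3-1.0) it does so in 39-99%.

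**The case against.** Four points can be made for the plan.

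- **Pretesting does no measurable harm here.** A reader might infer that choosing the test by pretests wastes power or inflates type I error. The calculations do not support either. What remains against the pretests is that they leave the primary contrast open.
- **Skewness of hs-CRP is not documented.** The article gives no SD, distribution or correlation. This stands: the size of the loss is conditional on assumed lognormality.
- **The large power gap is not at the planned effect.** A reader might take 0.65 as the protocol's figure, because SQSX is expected to leave 65% of baseline. That is a within-arm fraction; the between-arm ratio is 0.921, where both analyses have little power. This stands in full.
- **Other analyses are planned, and a statistical analysis plan may add detail.** The mixed model would give an effect estimate, and nothing bars a log scale for it, so it would be too strong to say that the trial will have no estimate. However, the mixed model is not named as primary. The endpoint scale and the selection rule are both stated in the article, so the objection is to what is written and not to an omission.

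**Conclusion.** The point holds in a limited form. It needs no assumption to say that the primary contrast is chosen from the trial data, is on a different scale from the percentage hypothesis, and has baseline adjustment only as a contingency. The power loss does need assumptions. If hs-CRP is roughly lognormal and the true effect is large enough to be detectable with 27 per arm, the plan's rule has roughly half the power of log-ANCOVA (32-44% where log-ANCOVA has about 80%). The cause is the raw scale and the unadjusted comparison.

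It would be tempting to conclude that a better test makes the trial adequately powered. The figures do not support that. At the ratio of 0.921, power stays at 5-11% for log SD 0.6-1.0, and reaches only 29% with log-ANCOVA in the most favourable setting tried (log SD 0.3, correlation 0.7). The sample size is a separate problem. This change should be made for clarity and efficiency.

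**What to change.** Drop the Shapiro-Wilk and Levene pretests as a way of choosing the primary test. Prespecify one primary analysis: ANCOVA of log hs-CRP at day 14 with treatment arm and log baseline hs-CRP as terms, whether or not baseline imbalance is seen. Report the SQSX/placebo geometric mean ratio with its 95% CI. Keep the Wilcoxon rank-sum test as a sensitivity analysis.

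The baseline term should be written in explicitly. At a ratio of 0.65, log SD 0.8 and correlation 0.5, an unadjusted day-14 log comparison has 48% power against 60% with the adjustment.

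The cost is a change of wording and no new data. The Trial Status section says that no analysis has been done, so the change can still be made credibly in advance. The small downside is that the result is a ratio and not a mg/L difference.

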### Inclusion Criteria

Subjects who meet all of the following criteria are eligible to participate in the study: (1) diagnosed as unstable angina (UA) or non-ST segment elevated myocardial infarction (NSTEMI) according to the 2015 ESC guidelines for the management of NSTEACS (22); (2) diagnosed as the TCM syndrome of Qi deficiency and blood stasis according to the Guiding Principles For Clinical Research Of New Chinese Medicines (23); (3) age 40–60 years; (4) heart function is Killip grade I-II for subjects diagnosed as NSTEMI; (5) in-hospital patients; (6) written informed consent is obtained.

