### Withdrawal, Dropout, and Discontinuation

Patients have the right to exit the study at any time. Dropouts and reasons for leaving will be documented in the case report form (CRF). Data on these participants will also be incorporated into the statistical analysis. The reasons for discontinuing the trial by the principal investigator are: (1) participant experiences more clinical complications or a serious adverse event; (2) financial and management reasons; (3) administrative authorities terminate the trial.

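### The hs-CRP change is tested without baseline adjustment unless an undefined imbalance is seen, which gives away precision that a pre-specified ANCOVA or mixed model would keep

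*Protocol article*

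**What the plan says.** All of this is in the Statistical Analyses section of the protocol article unless another section is named.

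- The primary outcome is "the change values of hs-CRP from recruitment to day 7 ± 3, day 14 ± 3 and the day of revascularization". This outcome and the SAQ change scores "are both continuous variables".
- The between-group test follows pre-tests for normality and equal variance: "A Student *t* test will be used to compare two groups that have a normal distribution with homogeneous variance, otherwise the Wilcoxon rank-sum test will" apply. Neither test includes a baseline covariate.
- Adjustment is conditional: "If there are baseline imbalances, Cox regression analysis, logistic regression and multivariate analysis of covariance will be used to adjust confounding variables". No definition of imbalance and no covariate list follow.
- Some variables may be dichotomised or grouped: "When some continuous variables are converted into categorical variables, these categorical variables will be described using rates". The article does not say which, and hs-CRP is not named among them.
- A further model is planned: "The longitudinal data with repeated measures will be analyzed using the linear mixed-effects model to assess associations". Its rank against the t test and its handling of baseline are not stated.

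Table 1 schedules hs-CRP at Visit 1, so every randomised patient should have a baseline value. Neither Outcomes Measures nor Table 1 contains a time-to-event outcome, and the Discussion leaves MACCE to a possible later investigation.

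**The concern.** Baseline hs-CRP is a natural predictor of later hs-CRP. Subtracting it, as a change score does, is the right correction only if the regression slope of follow-up on baseline is 1. With a lower slope, subtraction over-corrects. The arm that starts higher by chance then shows a larger fall from regression to the mean alone. With 27 evaluable patients per arm, such imbalances can be large enough to matter.

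Making adjustment depend on observed imbalance has two costs. The precision gain is lost in most trials, because adjustment is rarely triggered. And because the trigger is undefined, the estimator for the primary outcome can be chosen after the baseline data, or even the results, have been seen. The list of methods does not settle the matter, since two of the three cannot give an adjusted difference in a continuous hs-CRP change.

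**Working it through.** **Inputs from the protocol article.** Sample Size Calculation gives 27 per arm, 80% power, alpha 0.05, a control fall from 5.30 to 3.74 mg/L (29.43%) and a hypothesised 35% fall on treatment. Statistical Analyses gives two-sided testing. **Assumed, because the article does not give it:** the correlation rho between baseline and follow-up hs-CRP, taken as 0.3, 0.5 and 0.7.

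**The plan's own figure.** The 27 per arm cannot be reproduced, because no standard deviation is stated. The planned difference is 5.30 × 0.35 − (5.30 − 3.74) = 0.295 mg/L. Solving the article's formula backwards at two-sided alpha gives a standard deviation of about 0.37 to 0.38 mg/L. The total follows from 27 × 1.2 = 32.4, rounded up to 33 per arm, or 66. Below, 80% power for the change-score test at 27 per arm is taken as the article's premise and not as a verified figure.

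**Variance of the two estimators.** Let s² be the common variance at baseline and follow-up.

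- Change score, per patient: 2(1 − rho)s²
- ANCOVA, per patient: (1 − rho²)s²
- Ratio: (1 − rho²) / [2(1 − rho)] = (1 + rho)/2

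The direction does not need equal variances. With baseline SD s0 and follow-up SD s1, the change-score variance minus the ANCOVA variance is s0² + s1² − 2·rho·s0·s1 − s1²(1 − rho²) = (s0 − rho·s1)², which is never negative. This ignores the one degree of freedom spent on the slope.

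**Power at 27 per arm if the change-score test has 80%.** By normal approximation this is Φ[(1.96 + 0.842)/√ratio − 1.96].

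| rho | Variance ratio | Gain in effective n (1/ratio − 1) | n per arm for equal precision (27 × ratio) | Power, always ANCOVA (approx.) |
|---|---|---|---|---|
| 0.3 | 0.65 | 54% | 18 | 93% |
| 0.5 | 0.75 | 33% | 21 | 90% |
| 0.7 | 0.85 | 18% | 23 | 86% |

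**Simulation of the conditional rule.** This used 100,000 trials per setting, 27 per arm, normal data and equal variances. The article does not define the trigger, so it was assumed to be a baseline difference at p<0.05, met in about 5% of trials.

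| rho | Power: change t test | Power: adjust only if p<0.05 | Power: always ANCOVA |
|---|---|---|---|
| 0.3 | 79.9% | 81.3% | 93.0% |
| 0.5 | 80.0% | 80.9% | 89.3% |
| 0.7 | 80.1% | 80.6% | 85.2% |

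The conditional rule recovers almost none of the gain.

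**Type I error given imbalance.** With no treatment effect, the correlation between change and baseline is −√[(1 − rho)/2], that is −0.59, −0.50 and −0.39. A chance baseline difference therefore carries into the change score.

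| rho | Change test, baseline p<0.05 | ANCOVA, baseline p<0.05 | Change test, baseline p 0.05–0.3 |
|---|---|---|---|
| 0.3 | 23.9% | 5.1% | 8.5% |
| 0.5 | 18.3% | 5.3% | 7.5% |
| 0.7 | 11.9% | 5.2% | 6.9% |

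The last column covers imbalances that a p<0.05 trigger would pass over.

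**Overall type I error.** At rho 0.3, 0.5 and 0.7, a fixed p<0.05 trigger gives 4.1%, 4.4% and 4.7%. Free choice of the smaller of the two p-values gives 7.7%, 7.3% and 6.9%.

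**The case against.** The case on the other side has weight in several places.

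- *The listed models do fit.* A reader might infer that none of the named methods can give an adjusted hs-CRP difference. That is not so. Analysis of covariance fits a continuous outcome, and even a strict multivariate version yields adjusted differences outcome by outcome. Elsewhere in the same section the word multivariate is paired with univariate for regression models, so it may simply mean several covariates. The fault is that the method is conditional and loosely specified.
- *The sentence covers all outcomes.* This stands. Logistic regression can serve variables that are categorised. Only Cox regression is left without any outcome in the article.
- *Data-dependent adjustment inflates alpha.* A reader might infer this, but a fixed trigger does not inflate the overall error. Inflation needs a free choice between analyses. The article leaves that choice open, and a separate analysis plan may close it. The conditional rule itself, however, is written here and is not merely left to another document.
- *Dropouts.* The withdrawal section says "Data on these participants will also be incorporated into the statistical analysis". A t test of day-14 change cannot use a patient without a day-14 value unless one is imputed. It would still be too much to call this a contradiction. A mixed model that can use day-7 values is already planned, and imputation is commonly settled in the analysis plan.
- *Absolute power.* A reader might turn the variance ratio into a large power gain for this trial as planned. The article does not support that. The planned falls imply a between-arm ratio of only 0.65/0.706 = 0.92, and no standard deviation is given. The powers above hold only on the premise of 80% for the change-score test.
- *Diagnosis as covariate.* Nothing in the article shows that UA versus NSTEMI predicts hs-CRP, so the case rests on baseline hs-CRP alone.

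**Conclusion.** The point holds as one of efficiency and pre-specification. The default comparison of hs-CRP change omits a baseline covariate that is already collected, and the rule for bringing it in is undefined. Using it always would cut the variance to 65%, 75% or 85% of the change-score variance at rho 0.3, 0.5 or 0.7. It would also hold the type I error near 5% in trials with a baseline difference at p<0.05, where the unadjusted change test runs at about 24%, 18% or 12%.

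The sizes rest on an assumed rho, equal variances at the two times and normal data. They describe the t-test branch, not the Wilcoxon branch. That ANCOVA is at least as precise, apart from the one degree of freedom, does not depend on equal variances. hs-CRP may be skewed, in which case the same argument applies on the log scale. The findings do not show that the plan as written inflates the overall type I error or that it contains no usable model.

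**What to change.** For hs-CRP, replace the conditional sentence with one pre-specified analysis, fitted whatever the observed imbalance:

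- Use the linear mixed model already named, with treatment, visit, treatment by visit and baseline hs-CRP as covariate, or an ANCOVA at each time point with treatment and baseline hs-CRP. Use the log scale if hs-CRP is skewed, and fix that choice in advance.
- Report the adjusted difference at the time points that the protocol already states, including the day of revascularization. That day is not a scheduled visit in Table 1, so it may need its own ANCOVA. This change need not redefine the primary outcome.
- State that this model is the primary analysis and that the t or Wilcoxon test is supportive.
- Remove Cox and logistic regression for this outcome, and keep logistic regression only for categorised variables.
- Diagnosis (UA or NSTEMI) may be added as a covariate. This is optional and should be decided before unblinding.

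The cost is a text change, recorded as a dated amendment. No new data are needed, since hs-CRP is measured at Visit 1 and diagnosis is an entry criterion. Trial Status reports 20 completers, continuing recruitment and no analysis so far, so on the article's account the change could be made before any results are seen. If a patient leaves after Visit 2, the mixed model also uses that patient's day-7 value, in line with the withdrawal section.

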The Chinese herbal compound formula, Shenqisuxin granule (SQSX) is a novel patented drug (Chinese patent number ZL202010122712.6) for CAD. It comprises six herbs: Huangqi (Astragali Radix), Danggui (Angelicae Sinensis Radix), Danshen (Salviae Miltiorrhizae Radix Et Rhizoma), Ezhu (Curcumae Rhizoma), Huanglian (Coptidis Rhizoma) and Baizhu (Atractylodis Macrocephalae Rhizoma). Based on our previous pharmaceutical studies, the major ingredients of SQSX can activate phosphatidylinositol 3-hydroxykinase-protein kinase B (PI3K-Akt) signaling pathyway and elevate the expression of VEGF mRNA in ischaemic myocardium of rats to promote neovascularization and angiogenesis (17). It can regulate the expression of Ang1/Tie2 and Ang2/Tie2 in hibernating myocardium and promote neovascularization and maturation to improve cardiac function (18). It's also proven that the ingredients of SQSX inhibit the proliferation of vascular smooth muscle cells in the in-stent restenosis minipig model induced by balloon injury, thereby preventing in-stent restenosis (19). At a time when the treatment of NSTEACS has run into a bottleneck, SQSX is expected to provide an effective strategy for further improvement of NSTEACS. Thus, this study aims to examine the efficacy and safety of SQSX for NSTEACS and initially explore its mechanism.

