**Others**				
Adverse events			×	×
Drug distribution		×	×	
Medicine recycling			×	×

a) *General information includes: name, birth, sex, nationality, marriage and work, etc*.

b) *Safety indicators include: complete blood count, liver and kidney function tests, routine urine and stool tests*.

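### The only named between-arm comparison of adverse events is a Fisher test at P < 0.05, which says little about harm with 33 patients per arm; report the risk difference with its interval instead

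*Protocol article*

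**What the plan says.** The Introduction of the protocol article puts safety beside efficacy in the aim: "this study aims to examine the efficacy and safety of SQSX for NSTEACS and initially explore its mechanism". The Abstract and the Discussion repeat this.

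For adverse events, the Statistical Analyses section plans two things in one sentence. The first is descriptive: "The safety analysis will tabulate a detailed description of the adverse reactions, adverse events and serious adverse events". The second is inferential: "compare the difference in incidence between two groups using Fisher's exact probability method". The next sentence sets one threshold for everything: "0.05 at two-tailed test will be considered statistically significant in all analyses". Safety is not exempted.

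The notes to Table 1 add laboratory data, collected at baseline and day 14 ± 3: "Safety indicators include: complete blood count, liver and kidney function tests, routine urine and stool tests".

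Under Sample Size Calculation, "The sample size was estimated using hs-CRP". This gives 27 per arm, and 66 recruited in total after a 20% drop-out allowance. No adverse-event rate, safety margin or detectable difference in harm appears in the article.

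**The concern.** A significance test answers a useful question about harm only if it has a fair chance of detecting harm that matters. Here it is applied to a sample sized for a biomarker, and Fisher's exact test is conservative when counts are small. If events are uncommon, a non-significant result is the likely outcome whether or not SQSX raises their incidence substantially, so the P value barely separates the two situations.

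The study granule is added to aspirin, ticagrelor and enoxaparin, and the Discussion itself raises gastrointestinal bleeding and mucosal damage in this setting. The trial's statement on safety will therefore be read with interest. What is at stake is how informative that statement is. The hs-CRP conclusion is not affected.

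**Working it through.** **Inputs from the article.** 27 per arm required; 20% drop-out; 66 in total; 1:1 allocation; two-sided 0.05; Fisher's exact test on incidence.

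**Input not in the article.** The control-arm incidence of adverse events. It is assumed here, over 3% to 20%.

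**Step 1: the plan's own sample size.** 27 × 1.2 = 32.4, rounded up to 33 per arm, so 66 in total. This matches. (Dividing by 0.8 gives 33.75, so 34 per arm and 68 in total, two patients more; nothing below depends on the difference.) The figure of 27 cannot be recomputed, because no standard deviation is given.

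**Step 2: chance of missing a tripling.** For n per arm, control rate p and SQSX rate 3p:

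miss = 1 − Σ Bin(i; n, p) · Bin(j; n, 3p), summed over all count pairs (i, j) whose two-sided Fisher P is below 0.05.

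| Assumed control → SQSX rate | Missed, 33 per arm | Missed, 27 per arm |
|---|---|---|
| 3% → 9% | 97% | 99% |
| 5% → 15% | 88% | 93% |
| 10% → 30% | 58% | 69% |
| 15% → 45% | 31% | 42% |
| 20% → 60% | 10% | 20% |

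**Step 3: how conservative the test is.** The same enumeration with equal rates in both arms, 33 per arm, gives an actual false-positive rate of 0.2% at a common rate of 5%, 1.2% at 10% and 2.4% at 20%, against the nominal 5%.

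**Step 4: what particular results would show (33 per arm).**

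- 5 SQSX events against 0. Two-sided Fisher P = 2 · C(33,5)/C(66,5) = 2 × 237,336/8,936,928 = 0.053, so not significant. The risk difference is 5/33 = 15.2 points. The Wilson limits are 6.7% to 30.9% for SQSX and 0% to 10.4% for control. Newcombe lower limit: 15.2 − √((15.2 − 6.7)² + (10.4 − 0)²) = about +2 points. Upper limit: 15.2 + √((30.9 − 15.2)² + 0²) = about +31 points.
- 8 against 2. P = 0.08; Newcombe interval about +0.5 to +36 points.
- 9 against 3, an observed tripling. P = 0.11; interval about −0.8 to +36 points.
- With no control events, 6 SQSX events are needed to reach P < 0.05.

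**Step 5: no events in an arm.** The exact upper limit of the two-sided 95% interval is 1 − 0.025^(1/33) = 10.6%.

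**The case against.** Several points on the other side are right and limit the finding.

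- A reader might infer that a non-significant test would be taken as proof of safety. The article states no such rule; it only defines what is called statistically significant.
- A reader might also infer that safety rests on Fisher's test alone. It does not: the same sentence plans a detailed tabulation, and laboratory indicators are collected at two visits. The accurate statement is that Fisher's test is the only named between-arm comparison of adverse-event incidence. The tabulation describes events but gives no uncertainty for the difference between arms.
- It is tempting to quote a general miss rate of roughly 60 to 90%. That band belongs to assumed control rates of about 5 to 10% with 33 per arm. At 20%, a tripling would usually be found.
- The larger studies announced in the Discussion are not conditional on this trial's safety result, so they cannot be said to hang on this test.
- Low power for adverse events is usual in a trial of 66, sizing on the primary outcome is standard, and the Discussion lists the small sample as its first limitation. That limitation is general, however; it does not change how the safety P value is to be read.

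The strongest remaining objection is that interval methods are commonly left to a full protocol or analysis plan. That would settle the matter if the article were silent. It is not: it names a test and applies a threshold to safety along with everything else, and that stated choice can be improved. Fisher's test is valid for sparse counts. The criticism is of its role, not its correctness.

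**Conclusion.** The point holds as a weakness in a stated analysis choice, not as an error of calculation or a false claim of safety. With 33 per arm, the chance that the planned test misses a tripled incidence is 88%, 58%, 31% and 10% for assumed control rates of 5%, 10%, 15% and 20%. If only 27 per arm are evaluable, these become 93%, 69%, 42% and 20%. The size therefore depends on a control rate that the article does not give: the concern is serious for uncommon events, as serious adverse events may be, and slight if overall incidence is 20% or more. Whatever the rate, the P value shows neither the direction nor the range of compatible differences, and results such as 5/33 against 0/33 would be labelled non-significant while the interval points to harm. Part of that disagreement arises because Fisher's test is conservative and the Newcombe interval is approximate, which is a further reason not to rest the reading on one threshold. This is a cheap improvement worth making.

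**What to change.** In Statistical Analyses, make the safety comparison each arm's incidence and the risk difference (SQSX minus placebo) with a 95% interval, by the Newcombe or Miettinen-Nurminen method, for adverse events, serious adverse events and adverse reactions. Where an arm has no events, give the exact upper bound; 0/33 still allows 10.6%. Keep Fisher P values as descriptive only, exempt safety from the sentence that applies P < 0.05 to all analyses, and state that non-significance will not be read as absence of harm.

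The cost is one or two sentences and a few table columns from data already collected, with no more patients or visits. Trial Status reports that no analysis has been done, so the change can be made before results are known. The downside is that the safety statement becomes visibly less reassuring.
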